**Secondary Efficacy Endpoint(s):**

SPECIFIC AIM 2: Examine the effect of a clinic-based CHW-led MI intervention vs UC on Socioeconomic & Psychosocial Determinants of Health. Social Determinants of Health (SDOH) are drivers of health disparities and evidence demonstrates improved SDOH leads to improved health outcomes. INSTACARE’s CHW intervention aims to address the negative SDOH impacting HIV health among participants. These determinants are assessed using the validate measures included in the INSTACARE Health Survey delivered at baseline, 6-months, and study exit.

## Statistical Analyses

### General Approach

Using a randomized parallel-controlled design, we will evaluate the effects of our CHW intervention on VL suppression among nonadherent or acutely infected PLH. Analysis will be led by [name].

- Preliminary Data Analysis: Initial data analyses will include (a) descriptive statistics across time points for all variables and (b) testing of distributional assumptions of all variables, including statistical tests for univariate/multivariate normality and visual inspection of distributions of all variables (graphical examination of data). Should significant deviations from normality occur, transformation of variables will be attempted.

- Missing Data: Missing data are a ubiquitous problem in HIV behavioral research, primarily due to dropping out and refusal. We will make every effort to minimize missing data. During the analytic phase, we will carefully assess missing data (whether missing occurs at random). Missingness patterns will be identified, and analyses will be conducted to determine if there is differential attrition by treatment arm, and if missingness is related to any of the covariates. If nonrandom missingness is of concern, it will be addressed by applying pattern-mixture, propensity score or related models so that bias effect can be assessed in sensitivity analyses.

### Analysis of the Primary Efficacy Endpoint(s)

As specified in the aims, the primary hypothesis test will compare the proportions achieving HIV viral suppression at 12 months across the two study groups. All treatment comparisons will be performed under the Intent-to-Treat (ITT) criterion in the sense that participants will be analyzed in the arm to which they were randomized, regardless of subsequent events. Using a logistic GEE model, a type III contrast between CHW and UC arms will be estimated in a model with a binomial distribution and logit link as implemented in SAS for the primary outcome. The GEE model will include both 12-month HIV viral suppression status, and HIV viral suppression status at 3 months intervals. However, the primary test of the hypothesis will be based on contrasts involving the 12-month proportions only. This model gains statistical power by pooling the error term across the four follow-up times (3, 6, 9, and 12 months) and is closer to an ITT approach than would be the analysis of 12-month events only. Univariate and multivariate models will be used to calculate odds ratios and corresponding 95% confidence intervals for associations between viral suppression at 12 months and two treatment arms, controlling for covariates such as sociodemographics and potential confounders. In addition, stratified analysis will be examined for gender, ethnic, and immigration status differences. Two-way interaction terms between various study variables and the study arms may also be included in the models. Standard diagnostic tools will be used to assess model fit. Missing data associated with drop out or any other cause will not be imputed in the primary analyses. If needed, alternative analyses may explore others model to account for such missing data such as last valued carried forward or multiple imputation.

### Analysis of the Secondary Endpoint(s)

We will test the secondary outcomes respectively. Those secondary outcomes that are binary will be tested as described for the primary hypothesis using a logistic regression; whereas those secondary outcomes that involve either continuous or ordinal variables will utilize the appropriate distribution and link functions. Note that the exact method of analysis will depend on the realized distribution of the particular outcome in this trial. For example, an expected count data variable may need to be modeled using a zero-inflated Poisson Regression rather than a Poisson regression if there are too many zero observations to fit the standard Poisson. If there is over-dispersion, a negative binomial (or zero-inflated negative binomial) regression may be appropriate. Models will be estimated with main effects for these variables, a main effect for randomization group, and an interaction between the particular variable and randomized group on the primary outcomes. In addition, we will also conduct sensitivity analyses to explore and determine the association of specific CHW strategies, and the frequency of these strategies, with outcomes. The impact of CHW services will be measured 1) by the way care is delivered (in-person, phone, text); 2) the type of support provided (health education, health system navigation, linkage to social services, empathy), and 3) the setting in which interactions occur (community, clinic, home, virtual). A Bonferroni correction will be applied to secondary outcomes. Mediation: Mediation will be tested using structural equation modeling with Mplus 8.7. These models estimate the effect of the intervention on the potential mediators from secondary outcomes (path a) and the effect of the mediator on the viral suppression outcome or next proximal intermediate outcome (path b). Longer mediation pathways can also be tested (e.g., a*b*c). There is significant mediation if the product of these two paths (a*b) is greater than zero. Statistical significance will be assessed using bias-corrected bootstrap confidence intervals on the product terms. This test is by far the most powerful test of mediation and can test multiple mediating pathways within a single structural model.

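### The secondary-endpoint section gives two conflicting models, and the only one with listed terms does not test the Aim 2 effect

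*Protocol*

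**What the plan says.** Aim 2 is set out in the Protocol under Statistical Hypotheses, Secondary Efficacy Endpoint(s): "Examine the effect of a clinic-based CHW-led MI intervention vs UC on Socioeconomic & Psychosocial Determinants of Health". The determinants come from the "INSTACARE Health Survey delivered at baseline, 6-months, and study exit", so two of the three measurements follow randomization.

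Analysis of the Secondary Endpoint(s) opens by testing the secondary outcomes themselves. "Those secondary outcomes that are binary will be tested as described for the primary hypothesis using a logistic regression"; "those secondary outcomes that involve either continuous or ordinal variables will utilize the appropriate distribution and link functions". Poisson, negative binomial and zero-inflated models are named for counts.

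The section then gives its only list of model terms: "Models will be estimated with main effects for these variables", together with "a main effect for randomization group, and an interaction between the particular variable and randomized group on the primary outcomes". It does not define which variables are meant, gives no time point, and does not call this a moderator analysis. A Bonferroni correction for the secondary outcomes is announced later in the same paragraph, without saying which model it applies to.

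Two other places matter. The mediation text returns to the secondary outcomes: "These models estimate the effect of the intervention on the potential mediators from secondary outcomes (path a"). Analysis of the Primary Efficacy Endpoint(s) already allows effect modification: "Two-way interaction terms between various study variables and the study arms may also be included in the models".

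**The concern.** Aim 2 asks whether the arms differ on each determinant, so the determinant must be the outcome and arm the predictor. The sentence that lists terms reverses this. The nearest antecedent for its variables is the secondary outcomes, and its dependent variable is the primary outcome. Someone writing analysis code from this section has two incompatible specifications and no rule for choosing between them.

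Two things are at stake. If the second model were taken as the Aim 2 test, the reported p-values would answer other questions: whether arm affects suppression at a given level of the determinant, and whether the determinant's slope on suppression differs by arm. And if follow-up survey values were entered, the arms would be compared within levels of something the intervention is designed to move, so the comparison would lose the protection of randomization.

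**Working it through.** **Step 1. The statements side by side.**

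| Place in the Protocol | Dependent variable | Arm enters as | Answers Aim 2? |
|---|---|---|---|
| Statistical Hypotheses, Aim 2 | Determinant | Effect of interest | This is the question |
| Secondary analysis, opening sentences | Secondary outcome | Contrast, as for the primary hypothesis | Yes |
| Secondary analysis, sentence listing terms | Primary outcome | Main effect plus interaction with the variable | No |
| Secondary analysis, mediation path a | Mediator from the secondary outcomes | Path a | Estimates it, but the stated significance test is on the product of paths a and b |
| Sample Size Determination, secondary outcomes | Secondary outcome | Standardized difference between groups | Consistent with the opening sentences |

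**Step 2. What each model tests.** Let S be the determinant, A the arm (1 = CHW, 0 = usual care) and Y viral suppression at 12 months.

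- Aim 2: δ = E(S | A=1) − E(S | A=0), with null hypothesis δ = 0.
- Second model: logit P(Y=1 | S, A) = β0 + β1·S + β2·A + β3·S·A.

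β1 is the association of S with suppression in usual care, β2 is the arm effect on suppression at S = 0, and β3 is the difference in slopes. The model conditions on S and says nothing about how S is distributed in each arm. The same β values are compatible with any δ, so no term tests δ = 0.

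**Step 3. The time point.** With baseline S, randomization makes S independent of A, and β2 and β3 compare randomized groups within levels of S. With 6-month or exit S, participants sharing a value of S are no longer comparable by randomization, and β2 leaves out any effect of arm that runs through S.

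**Step 4. Illustration only.** This shows what would happen if the second model served as the Aim 2 test. The 150 per arm and two-sided 0.05 come from Sample Size Determination. All effect sizes are assumptions. S = a·A + N(0,1); logit P(Y=1) = −1.1 + b·S, so suppression is 1/(1 + e^1.1) = 25% at S = 0, matching the Protocol's control assumption. Arm has no effect on Y except through S. There were 1,000 trials per row. The entries are rejection rates; at a true 5% their Monte Carlo standard error is √(0.05 × 0.95/1000) = 0.7 percentage points.

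| Assumed truth | S term | Arm term | Interaction | Direct comparison of S by arm |
|---|---|---|---|---|
| a = 0.4, b = 0 | 4.4% | 6.4% | 4.6% | 93.0% |
| a = 0, b = 0.6 | 88.7% | 6.6% | 4.1% | 5.6% |
| a = 0.4, b = 0.6 | 85.5% | 5.0% | 5.0% | 91.7% |

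Hand check of the direct comparison: 0.4/√(2/150) = 3.46; 3.46 − 1.96 = 1.50; Φ(1.50) = 93%.

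- Row 1: the Aim 2 alternative is true and no term of the second model responds.
- Row 2: the Aim 2 null is true and the S term rejects in 89% of trials, because S predicts Y.
- Row 3: arm raises the logit of suppression by 0.4 × 0.6 = 0.24 through S, but the arm coefficient averages 0.002, because S is a follow-up value held fixed.

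**Step 5. The Bonferroni family.** The Study Assessments table lists ten primary measures for Aim 2. Assuming one score each, ten direct contrasts give 0.05/10 = 0.005 per test. Adding the three secondary measures of Aim 1 gives 0.05/13 = 0.0038. If an interaction test per Aim 2 measure also counted, the ten measures would need 0.05/20 = 0.0025. The Protocol may leave the count to a statistical analysis plan. The difficulty is that its text points to two different kinds of test.

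**The case against.** The strongest reply is that Aim 2 already has a direct test. The opening sentences treat the secondary outcomes as dependent variables. Choosing a count distribution would make no sense if binary suppression were always the response. The secondary power statement is a difference between groups, and path a estimates the arm effect again. All of this stands. A reader might infer from the list of terms that Aim 2 is left untested, or that the simulated gap in rejection rates is power the trial will lose. The documents support neither: nothing says the second model replaces the first.

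Next, the sentence may simply be a supplementary moderator analysis of the kind the primary section permits, with baseline variables. That is possible, and in that form it would be valid. A reader might also infer that the plan definitely conditions on post-randomization values. It does not say so; that follows only if follow-up values are entered. But the sentence stands under the secondary endpoints, is not labelled moderation, and sets no limit to baseline.

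Third, the drafting is loose. Primary outcomes appear in the plural although the trial names one, and the Study Assessments table also uses the word primary for Aim 2 measures. This argues against firm conclusions about intent, but it adds to the ambiguity.

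Finally, visit terms and covariates are commonly left to a statistical analysis plan. That is fair. The point here is a conflict in what the Protocol does state.

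**Conclusion.** The point holds as a conflict between two specifications in one section. The opening sentences answer Aim 2. The only sentence listing terms describes a model in which no term tests the CHW effect on a determinant. Two matters are left open: whether the interacting variables are baseline values, and which model feeds the Bonferroni-corrected tests.

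That the second model does not contain the Aim 2 parameter follows from its form and needs no assumed effect size. The reading of its variables as the secondary outcomes rests on the nearest antecedent. The post-randomization problem is conditional on using 6-month or exit values. The simulated rates rest on assumed effects and measure only a misuse the Protocol does not prescribe. The primary comparison is unaffected. The wording should be corrected before analysis.

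**What to change.** 1. State that for Aim 2 each survey measure is the dependent variable, that the test is the CHW versus usual care contrast at 12 months adjusted for that measure's baseline value, and that the Bonferroni correction applies to these contrasts. Keep the count models already named for record-based outcomes such as hospitalizations.
2. Delete the interaction sentence. Alternatively, relabel it as an exploratory moderator analysis with 12-month viral suppression as the outcome and arm, the baseline value of the variable and their interaction as predictors. Say that post-randomization values enter only the mediation model.

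The cost is a few lines of Protocol text, carried into any statistical analysis plan. The baseline survey is already collected, so no visit, measurement or participant is added.

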# SUPPORTING DOCUMENTATION AND OPERATIONAL CONSIDERATIONS

## Regulatory, Ethical, and Study Oversight Considerations

### Informed Consent

#### Consent Procedures and Documentation

Informed consent is a process that is initiated prior to the individual’s agreeing to participate in the study and continues throughout the individual’s study participation. Consent forms describing in detail the study intervention, study procedures, and risks are given to the subject and written documentation of informed consent is required prior to conducting enrollment procedures.

CHWs will explain the research study to the subject and answer any questions that may arise. A verbal explanation will be provided in terms suited to the subject’s comprehension of the purposes, procedures, and potential risks of the study and of their rights as research subjects. Subjects will have the opportunity to carefully review the written consent form and ask questions prior to signing.

The subject must sign the informed consent document prior to any procedures being done specifically for the study. Subjects must be informed that participation is voluntary and that they may withdraw from the study at any time, without prejudice. A copy of the informed consent document should be offered to the subjects for their records. The rights and welfare of the subjects will be protected by emphasizing to them that the quality of their medical care will not be adversely affected if they decline to participate in this study.

### Confidentiality and Privacy

Subject confidentiality and privacy are strictly held in trust by the participating investigators and their staff. Therefore, the study protocol, documentation, data, and all other information generated will be held in strict confidence. No information concerning the study or the data will be released to any unauthorized third party without prior written approval of the Principal Investigator.

Data will be collected from the EMR or subjects at UHealth or JHS.

In compliance with HIPAA, individual subject confidentiality is assured through the use of unique study identification codes throughout the processing and analyses. Physical and electronic study subject research data used for purposes of statistical analysis and scientific reporting, will be stored at the INSTACARE Research Office based at the University of Miami Miller School of Medicine. Electronic data is stored on a University of Miami electronic device (e.g. encrypted, password-protected computer) and on a cloud-based storage system that is approved by the University of Miami (e.g. the University’s REDCap data management system, which is backed up to University servers daily). These records will not include the subject’s contact or identifying information. Rather, individual subjects and their research data will be identified by a unique study identification number. The study data entry and study management systems used by research staff will be secured and password protected. Staff are provided with University-issued computers, tablets, and mobile devices equipped with password-protection and University-issued encryption.

At the end of the study, all records will continue to be kept in a secure location for as long a period as dictated by the reviewing IRB and/or Institutional policies.

### CHW Training

**FL Department of Health HIV Counselor Training**

1. **500 & 501 Online Training:** The FDOH HIV Counselor Training includes two online courses and an “in-person” (virtual) workshop.
2. The online training modules are provided by the Florida Department of Health through the TRAIN Florida Learning System. Please create a TRAIN Florida Account at <https://www.train.org/florida/user/register> to complete the courses.
3. Once you have an account, search for **FDOH HIV 500** or [click](https://www.train.org/florida/course/1050497/compilation) here to link to the course.
4. Select the registration tab to sign up for the course sessions. The 500 course has 5 sections, plus a learner’s guide and introduction, and each section has a short quiz at the end.
5. Once you complete 500, you’ll be able to register for 501. Click [here](https://www.train.org/florida/course/1058541/compilation) to link to the 501 course.
6. The 501 course has 6 sections, plus the learner’s guide and introduction, and each section has a short quiz at the end.
7. When you finish the training, download and sign the [500/501 Participation Agreement](https://www.testmiami.org/documents/500-501-participant-agreement.pdf). Please send a copy of the agreement and your certificates of completion to the Research Cooridnator & Program Manager.
8. ***In-Person (Virtual) Workshop:*** Once you complete the two courses, you can register for the two-day virtual workshop at <https://www.testmiami.org/forms/500-501.html>.
9. Before registration, confirm the registration dates with the Program Manager via email.
10. Once the date is confirmed, email your certificates to the FDOH HIV Program Consultant ([name]: [contact]). [name] will then send back a link with the available The workshop is a video conference call from 9am-1pm.
11. [name] will send you a list of available dates to choose from once she’s received your 500/501 certificates. For more details on the FDOH training, click [here](https://www.testmiami.org/providers.html#:~:text=TRAININGS,501%20Participant%20Agreement).

**CITI Training**

***Collaborative Institutional Training Initiative (CITI):*** <https://www.research.miami.edu/about/admin-areas/raa/coi/citi/index.html>

The Collaborative Institutional Training Initiative (CITI Program) site offers web-based training in research compliance and ethics. CITI training is mandatory for all members of the research team.

**Login Instructions**:

1. Click on the “Login to CITI Program Using CaneID”
2. The CaneID Authentication Service page will appear
3. Enter your CaneID and Password and click on the “Sign In” button

***Note****: If this is the first time you have ever logged into CITI Program, a new CITI Program account is created for you.*

[Login to CITI Program Using CaneID](https://www.citiprogram.org/Shibboleth.sso/Login?target=https%3A%2F%2Fwww.citiprogram.org%2FSecure%2FWelcome.cfm&entityID=https%3A%2F%2Fcaneid.miami.edu%2Fidp%2Fshibboleth)

1. If you do not see the course you need, click on “Add or Update Learner Groups” in the University of Miami / Jackson Health System section of your CITI Program gradebook. This link is in the “My Learner Tools” section of the gradebook.
2. Complete the following course(s):
3. **Human Subjects Research Series (Question 3)**
   - ***Group 2: Social-Behavioral Researchers Basic Course (Question 8)***

**Motivational Interviewing**

CHWs will receive an introduction to Motivational Interviewing theory and practice specifically for HIV health care workers. The training series provides a didactic overview of the MI process and its practice, by the demonstration of MI, guided role playing of MI, evaluation of MI skills employed by self and colleagues, independent practice of MI, and coaching by MI instructors.

Below is the breakdown of the workshop series trainings and assignments:

| **Session** | **Session Topics** | **Homework** | **Skills Practice** |
| --- | --- | --- | --- |
| **1** | What is MI  MI in Healthcare/ HIV care  Spirit of MI (Compassion, Acceptance, Evocation & Collaboration/Partnership)  Process of MI (Engaging, focusing, evoking, planning) | Miller & Rollnick  pp.1-105 | Identify MI skills  (Observation & identification) |
| **2** | Focusing (Following, guiding, directing)  Tools of MI  Goal setting  Evoking (Ambivalence)  Demonstration of MI | Miller & Rollnick  pp. 106-180; pp. 181-210  List of personal & actual behavior changes due @ Session 3 | Practice Engaging  Practice Focusing  Practice Goal setting  Practice Evoking |
| **3** | Planning  Using MI to change behavior  Change talk/sustain talk/discord  Integrating MI in your visit | Miller & Rollnick  pp 211-290; pp 291-393  Standard practice /role play recording due @ Session 4 | Practice MI planning  Practice MI integration |
| **4** | Experiencing MI  MI fidelity- Self-awareness/coding  Training & Supervision | Miller & Rollnick  pp 368-369  Post-training patient consultation recording due 2-wks after Session 4 | Practice MI integration  Practice MI evaluation |

### Quality Assurance and Quality Control

The site will perform internal quality management of study conduct, data collection, documentation and completion. Quality control (QC) procedures will be completed by the Data Manager on a quarterly basis. Any missing data or data anomalies will be communicated to the Research Coordinator and CHWs for clarification/resolution. The site will provide direct access to all trial related sites, source data/documents, and reports for the purpose of monitoring and inspection by local and regulatory authorities.

